**Methods/Design:**

This study, an unblinded randomized controlled trial, will evaluate the effectiveness and cost of Elder Tree. Older adults who are at risk for losing their independence - along with their informal caregivers, if they name them - are randomized to two groups. The intervention group has access to their usual sources of information and communication as well as to Elder Tree for 18 months while the control group uses only their usual sources of information and communication. The primary outcome of the study is older adult quality of life. Secondary outcomes are cost per Quality-Adjusted Life Year and the impact of the technology on independence, loneliness, falls, medication management, driving and transportation, and caregiver appraisal and mastery. We will also examine the mediating effect of self-determination theory. We will evaluate the effectiveness of Elder Tree by comparing intervention- and control-group participants at baseline and months 6, 12, and 18. We will use mixed-effect models to evaluate the primary and secondary outcomes, where pretest score functions as a covariate, treatment condition is a between-subjects factor, and the multivariate outcome reflects scores for a given assessment at the three time points. Separate analyses will be conducted for each outcome. Cost per Quality-Adjusted Life Year will be compared between the intervention and control groups. Additional analyses will examine the mediating effect of self-determination theory on each outcome.

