**Table 3 Tab3:** **Outcome and other measures**

**Outcome measures**									
**Construct/Associated Hypothesis** ^**a**^		**Instrument**	**Burden**	**When**					**Who**
				**S**	**B**	**6**	**12**	**18**	
Primary outcome:									
Quality of life: Global Mental Health and Global Physical Health/1		PROMIS Global Health [39]	10		X	X	X	X	OA
									CG
Secondary outcomes:									
Independence: Activities of Daily Living (ADLs) and Instrumental Activities of Daily Living (IADLs)/2		Getting to places outside the home, moving/walking around the home, taking your medications, planning and preparing meals, bathing and using the toilet, dealing with finances [53-55]	6		X	X	X	X	OA
Cost per Quality-Adjusted		QALY: PROMIS Global Health converted to QALYs using EuroQol-5D (EQ-5D) [40]	0		X	X	X	X	OA
									CG
Life Year (QALY)/3									
		Intervention cost: modified DATCAP [41]	0			X		X	OA
									CG
		Healthcare utilization: patient survey using modified medical services utilization form [43]	6		X	X	X	X	OA
									CG
Loneliness/4		UCLA Loneliness Scale (Version 3) [56]	20		X	X	X	X	OA
									CG
Falls/5		Recent falls: # of falls; # requiring medical attention	2		X	X	X	X	OA
		Falls risk: Falls Behavioral Scale for the Older Person (FaB) (modified) [57]	15		X	X	X	X	
Medication management/6		Presence of risky medication: status of taking blood thinners, insulin, or oral medications for high blood sugar or diabetes [58]	3		X	X	X	X	OA
		Medication adherence: to what extent would you estimate that you take your medication doses?	1		X	X	X	X	
		Medication side effects: presence or absence of common side effects of antiplatelets/anticoagulants and insulin/oral hypoglycemics [59]	18		X	X	X	X	
Ease of driving and transportation/7		Ease of/comfort with transportation; # of crashes and near-misses	7 to 12		X	X	X	X	OA
Caregiver appraisal, burden, satisfaction with relationship, and mastery/8		Lawton Caregiving Appraisal Scale [60]	19		X	X	X	X	CG
Caregiver coping: wishfulness, acceptance, intra-psychic, instrumental/9		Caregiver Coping Strategies [61]	16		X	X	X	X	CG
Mediators: three constructs of self-determination theory		Autonomy: *Survey:* How well do you carry out social activities and roles; do you currently drive? *Elder Tree use data:* # and extent of services used.	2		X	X	X	X	OA
									CG

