		Competence: *Survey:* To what extent can you carry out everyday activities; IADLs, comfort with technologies)? *Elder Tree use data:* # of informational pages and tips viewed.	3		X	X	X	X	OA
									CG
		Relatedness: *Survey:* selected items from the MOS Social Support Survey (MOS-SS) (modified) [62] related to how often someone is there to *provide* support to and *receive* support from you, plus how often you have participated in a health or medical support group or social club or group? *Elder Tree use data:* # of emotionally supportive messages posted and read	17		X	X	X	X	OA
									CG

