**Measures related to other challenges**									
**Challenge**	**Construct**	**Instrument**	**Burden**	**When**					**Who**
				**S**	**B**	**6**	**12**	**18**	
Social con-nectedness	Online bonding	CHESS Bonding Scale	4		X	X	X	X	OA
									CG
	Size of social network	# of people to listen to you, to whom you listen, from whom you get help, show love, get together to do something enjoyable	5		X	X	X	X	OA
	Other support	Types of therapy or support groups	6		X	X	X	X	OA
									CG
Service delivery	Satisfaction with service delivery	Showering/bathing/grooming; in-home meal prep or Meals on Wheels; toileting and incontinence; medical support services	4		X	X	X	X	OA
									CG

^a^Hypotheses: compared with the control group, at 6, 12, and 18 months, those randomized to Elder Tree will experience:

1. Improved quality of life (older adults).

2. Improved independence (older adults).

3. Lower healthcare cost per QALY (older adults).

4. Less loneliness (older adults).

5. Fewer falls (older adults).

6. Improved medication management (older adults).

7. Greater ease of transportation and driving (older adults).

8. Improved caregiver appraisal (caregivers).

9. Increased coping strategies (caregivers).

Mediation hypothesis: SDT (autonomy, competence, relatedness) will mediate the effects of Elder Tree on older adult outcomes.

S, screening; B, baseline; OA, older adult; CG, caregiver.

CHESS, Center for Health Enhancement Systems Studies at the University of Wisconsin-Madison, WI, USA; DATCAP, Drug Abuse Treatment Cost Analysis Program; MOS; Medical Outcomes Study; PROMIS, Patient-Reported Outcomes Measurement Information System.

We are also collecting data on the server about how participants use Elder Tree. We use this information to monitor the functioning of the website - for example, see if the website has problems. These use data also will be analyzed after the randomized trial to explore such questions as whether participants who used Elder Tree the most had better outcomes.

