#### Measures related to caregivers and mediation

Two instruments will assess the results of using Elder Tree on caregivers. A combination of survey items and Elder Tree use data will assess the mediating effect of the three constructs of SDT. Computer-aided content analyses of discussion group posts will be used to explore the relationship between the reception and expression of emotional content and outcomes.

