### Data analysis

We will evaluate the effects of Elder Tree by comparing intervention and control participants at 6-, 12-, and 18-month assessments. We will use mixed-effects models to evaluate our primary and secondary hypotheses, where pretest score functions as a covariate, treatment condition is a between-subjects factor, and the multivariate outcome reflects scores for a given assessment across the 3 time points (months 6, 12, and 18). Separate analyses will be conducted for each outcome.

We will use path analysis to test whether the constructs of SDT mediate the relationship between Elder Tree and participants’ QOL at 6, 12, and 18 months. Mediation will be tested based on the significance and size of the specific indirect effects of system use through SDT constructs on relevant outcomes [49-51], as well as the overall fit of the model. Overall model fit will be assessed with statistics traditionally used for this task (for example, CFI, TLI, RMSEA).

Secondary analyses will lend further insight related to primary hypotheses’ findings. The intercorrelations between studied outcomes (for example, Instrumental Activities of Daily Living (IADLs), QOL) and mediator (SDT) will clarify whether these outcomes represent unique versus highly-correlated outcomes. Additional analysis will disaggregate overall Elder Tree effects into component services. Given the non-random selection of services and the potential correlation between the use of certain services, this analysis will address whether a service was used and the intensity of that use. This should reduce multi-collinearity issues in regression analysis and provide insights into each service’s contributions. Outcomes associated with specific Elder Tree services will also be compared between users and non-users of specific services in an exploratory Complier Average Causal Effect (CACE) analysis to examine whether actual use of a service (rather than randomized access to it) is associated with improved outcomes. We will also examine trends within groups over time (for example, whether gains from Elder Tree at 6 and 12 months are maintained to 18 months).

Because we anticipate that Elder Tree will take at least 3 months to have an effect, we plan to conduct exploratory analyses that mirror the aforementioned analyses but exclude participants who die or move to a nursing home or assisted living facility within the first 3 months of the intervention.

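### The mediation test takes self-selected system use as its exposure, lists Elder Tree log counts under every mediator, and shares IADLs with the independence outcome, so it can show mediation where there is none

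*Protocol article*

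**What the plan says.** All references are to the Protocol article.

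- **Aim.** The path analysis planned in the Data analysis section has this purpose: "test whether the constructs of SDT mediate the relationship between Elder Tree and participants’ QOL at 6, 12, and 18 months". The mediation hypothesis under Table 3 is broader: "SDT (autonomy, competence, relatedness) will mediate the effects of Elder Tree on older adult outcomes". The Abstract is broader still: "Additional analyses will examine the mediating effect of self-determination theory on each outcome".
- **Test.** The next sentence of the Data analysis section bases the test on the significance and size of the "specific indirect effects of system use through SDT constructs on relevant outcomes", together with overall model fit.
- **Mediators.** The section on measures for caregivers and mediation says: "A combination of survey items and Elder Tree use data will assess the mediating effect of the three constructs of SDT". Table 3 gives each construct a survey part and a use-data part. For autonomy, the use data are the number "and extent of services used". For competence they are informational pages and tips viewed, and for relatedness emotionally supportive messages posted and read.
- **Shared variable.** The competence survey items are "To what extent can you carry out everyday activities; IADLs, comfort with technologies". Secondary outcome 2 in the same table is "Independence: Activities of Daily Living (ADLs) and Instrumental Activities of Daily Living (IADLs)/2".
- **Controls.** They have only their usual sources of information and communication, not Elder Tree.

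**The concern.** There are three separate problems.

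1. **Exposure.** The hypothesis concerns what Elder Tree does, which randomization can answer. The test concerns what using it does. Use is decided after randomization by participants whose health, mood and social life may also shape their SDT answers and their outcomes. The article acknowledges non-random selection of services, but only for the service-level analysis.
2. **Use on both sides of the first path.** Log counts are zero or undefined in every control. Once they enter a mediator, the path from exposure to mediator is partly use predicting use, and it differs between arms whether or not autonomy, competence or relatedness changes.
3. **Outcome inside the mediator.** When independence is modelled, IADLs are in both the competence mediator and the outcome, so the outcome partly mediates itself.

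At stake is the claim about why Elder Tree works. SDT is presented as the foundation of the intervention, and a positive mediation result would be read as support for it. The fit indices named in the plan give no protection in the simple exposure-mediator-outcome model: it is just identified and fits perfectly whatever the truth.

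**Working it through.** The plan states no figure for the mediation analysis, so there is none to reproduce. The Sample size section gives the number analysed: 450 × 0.80 = 360, or 180 per arm. Everything else below is an assumption made for illustration.

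**A. Quality of life, with no mediation present**

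A trait u with loading c drives use, the SDT survey score and quality of life (QOL); e is independent standard normal noise.

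- Survey score = c·u + √(1−c²)·e, and QOL likewise. Elder Tree affects neither, and the survey score does not affect QOL.
- Use = arm × max(0, 1 + c·u + √(1−c²)·e). Log count = arm × max(0, use + 0.5·e), standardized.
- Composite mediator = (survey score + log count)/2.
- Mediation is declared when the exposure-mediator and mediator-outcome paths both have |t| > 1.96. There were 3,000 runs.

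False-positive rates:

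| Exposure | Mediator | c = 0 | 0.3 | 0.5 | 0.7 |
|---|---|---|---|---|---|
| Use, all participants | survey + log | 4.8% | 32.3% | 98.4% | 100% |
| Randomized arm | survey + log | 6.0% | 48.3% | 99.9% | 100% |
| Use, all participants | survey only | 0.3% | 5.7% | 69.7% | 99.9% |
| Use, Elder Tree arm only | survey only | 0.2% | 4.6% | 72.1% | 99.8% |
| Randomized arm | survey only | 0.1% | 1.9% | 5.3% | 5.3% |

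The first row is closest to the text. A repeat with fresh random numbers (2,000 runs) gave 5.2%, 35.0% and 98.8% for that row at c = 0, 0.3 and 0.5, and 5.6%, 50.6% and 100% for the second row. Only the last row stays near or below 5% throughout.

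**B. Independence: IADL overlap alone**

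Let Y be the outcome with arm effect δ, X1 and X2 two other competence items independent of everything, and M = (Y + X1 + X2)/3, all with unit variance within arm.

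- a = δ/3. With δ = 0.3, a = 0.1.
- b = Cov(M, Y)/Var(M) within arm = (1/3)/(3/9) = 1.
- ab = 0.1, and 0.1/0.3 = 33% of the effect appears mediated although no pathway exists.

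In simulation this indirect effect is significant in about 38% of trials when δ = 0.3 and in 4% to 5% when δ = 0. Overlap alone therefore distorts the estimate but does not guarantee significance.

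**C. Independence: IADL overlap plus log count**

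Let M = (Y + X1 + X2 + L)/4, where L is the standardized log count. There is no effect on Y and no common trait. In this set-up L differs between arms by about 1.31.

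- a = 1.31/4 = 0.33, from L alone.
- Within-arm variance of L = 1 − 1.31²/4 = 0.57.
- b = (1/4)/((3 + 0.57)/16) = 4/3.57 = 1.12, from Y being inside M.
- ab = 0.33 × 1.12 = 0.37, offset by a direct effect of −0.37, so the total is zero.

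The simulated false-positive rate (2,000 runs) is 100% with use as exposure, whether L has full or half weight. With arm as exposure it is 100% at full weight, and 86% to 95% at half weight in two separate runs. Randomized arm with a survey-only mediator and IADLs removed gives 0.2% to 0.4%.

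**The case against.** The best defence is that the article does not say how the parts are combined. Table 3 labels survey items and use data separately under each construct. Nothing says they are averaged, or that logs enter a two-arm model. Scoring is detail that a condensed article leaves to the analysis plan. The wording also fits a model of use, survey SDT score and outcome within the Elder Tree arm, where missing control logs would not matter.

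This stands in part. The averages in A and C are assumptions. But the exposure is stated, and the use data are said to be combined with survey items in assessing mediation, so an analysis plan would have to override this text, not just fill it in. The within-arm reading leaves use self-selected: at c = 0.5 it still gives 72% false positives.

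The Data analysis section names QOL first, and IADLs are not the QOL measure. That is correct, and the overlap does not touch the QOL path. But the Abstract and the hypothesis under Table 3 extend mediation to the other outcomes without excluding independence. The plan to examine intercorrelations between outcomes and the mediator may reveal the overlap but does not remove it.

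Three stronger readings are tempting and not supported:

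- **That significant indirect effects are guaranteed by construction.** For QOL the logs secure only the first path. Without a common trait the rate is about 5%.
- **That the SDT hypothesis cannot be tested in this trial.** Survey items are scheduled for older adults at baseline and months 6, 12 and 18 with no restriction by arm, and the first mediation sentence allows an arm contrast.
- **That driving is on both sides as IADLs are.** The autonomy item asks whether the person drives now. The outcome is ease or comfort with transportation, and crashes and near-misses. This is a shared domain, not a shared variable.

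**Conclusion.** The point holds for the indirect effects as the article specifies them. The exposure is not the randomized one, use is also listed under every mediator, and IADLs are in both the competence mediator and the independence outcome.

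The size depends on the outcome. For QOL, false mediation runs from about 5% with no common trait, through roughly a third to a half at a loading of 0.3, to near 100% at 0.5. The loadings are assumed and the documents give no information on them. For independence, false mediation is near certain if logs and IADLs are averaged into competence, with or without a common trait. That rests on assumed weights and independent items.

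This is a supplementary mechanism analysis. The primary and secondary comparisons between arms are unaffected. The change should be made, but the trial's main conclusions do not depend on it.

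**What to change.** Amend the mediation paragraph and the mediator rows of Table 3, or have the analysis plan explicitly override them:

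1. Make randomized arm the exposure.
2. Define autonomy, competence and relatedness only from survey items asked in both arms.
3. Remove IADLs from competence when independence is the outcome.
4. Adjust for the baseline mediator and the baseline outcome.
5. Report use-based analyses separately, labelled exploratory and confined to the Elder Tree arm.

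Using an earlier mediator to predict a later outcome is optional. It clarifies time order but gives up the month-6 estimate that the article plans.

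The cost is wording only, since the survey items are already scheduled at baseline and every follow-up. Mediator scales become shorter. Randomizing the exposure does not randomize the mediator, so the mediator-outcome path remains observational and should be reported as such.

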### Randomization

The project statistician used a computer-generated allocation sequence to randomize eligible older adults (or older adult/caregiver dyads) in a 1:1 ratio to intervention (Elder Tree) or control. Randomization is stratified by geographic region, whether a participant has his or her own computer or other device, and living alone, using random blocks of 4 and 6. Randomization is implemented by the project director using sequentially numbered, sealed, opaque envelopes. The sequence is thus unknown to the county coordinators who enroll participants. Because of the nature of the intervention, neither participants nor research staff are blinded to allocation.

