## Discussion

The development and testing of Elder Tree mark several important advances. Very few technologies have been designed for or rigorously tested with older adults, who often have physical and cognitive limitations not common among younger people. Elder Tree has been developed with the deep involvement of older adults. The technology also has been developed by working closely with community and state partners, such as local Aging and Disability Resource Centers and the Wisconsin Bureau of Aging, both to create a technology that is adaptable to different communities and to build a base for dissemination. Because we will be able to relate outcomes to use of the system, we also hope to understand why and how the system works or does not work and for whom.

Elder Tree is a multifaceted intervention with interacting services. For example, better medication management as a result of using Elder Tree may reduce the risk of falling. These interactions may make it challenging to assess which services or combination of services in Elder Tree account for changes in outcomes. Settling on our recruitment criteria has been an unexpected challenge because our original inclusion criteria proved to be too restrictive.

We have undertaken an active dissemination campaign in Wisconsin from which we hope to learn about effective ways to promote the use of technology among older adults, including those who have not used computers before. By piloting dissemination during the randomized trial phase, we are learning what communities will need to be able to adapt and maintain Elder Tree for their residents and what types of community organizations may want to provide it and why. This early dissemination work will accelerate the transition from research to practice should the randomized trial show positive results.

If Elder Tree can improve the quality of life of older adults and reduce healthcare costs, it could suggest one path to significantly reducing the physical, emotional, and financial burdens that advancing age can place on older adults, their families and communities, and the healthcare system.

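### The exploratory per-service CACE is described as a comparison of users with non-users, which is an as-treated contrast; one randomization to the whole system does not identify a complier effect for each service

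*Protocol article*

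**What the plan says.** The relevant text is in the protocol article.

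- **Data analysis, the contrast.** Service-specific outcomes will be "compared between users and non-users of specific services in an exploratory Complier Average Causal Effect (CACE) analysis".
- **Data analysis, the aim.** The purpose is "to examine whether actual use of a service (rather than randomized access to it) is associated with improved outcomes".
- **Data analysis, the preceding sentences.** The planned breakdown of the overall effect into component services is introduced with "Given the non-random selection of services and the potential correlation between the use of certain services".
- **Randomization.** Older adults, or older adult and caregiver dyads, are allocated "in a 1:1 ratio to intervention (Elder Tree) or control". No service is randomized separately.
- **Abstract, Methods/Design.** For comparison, "the control group uses only their usual sources of information and communication", so controls are not meant to use any service.
- **Discussion.** "Elder Tree is a multifaceted intervention with interacting services", and the article accepts that attributing changes to particular services may be difficult.

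For the analysis called CACE, the article names no instrument, exclusion assumption or principal-stratum model.

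**The concern.** The name and the described comparison belong to different estimands. In a complier analysis the randomized arm is the instrument: people who would use the service if offered it are compared across arms, and those people cannot be directly observed among controls. A split by observed use discards randomization and compares people who differ in interest, health and ability.

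The article itself shows that use depends on such things. Under Intervention, content is tailored to health conditions, with diabetic users receiving material from the diabetes coach. In Table 1, users decide which health measures to track, if any.

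A second problem would remain if the analysis were run with arm as instrument. Assignment opens discussion groups, coaches, trackers and tools at once. It can therefore change an outcome by routes other than the service under study, and the exclusion restriction fails service by service.

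At stake is the reading of the result. A figure labelled as a complier average causal effect invites the conclusion that a given service works, when it may only show who chose it or what the rest of the system did.

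**Working it through.** **The plan's own figure.** The article gives no number for this analysis. The nearest is the revised target under Sample size: 225 per group, d = 0.3, 80% power, 80% response. With a two-sided 5% level (assumed; not stated), 175 per arm are needed. 175 / 0.80 = 219 per arm, or 438 in total, within 3% of the stated 450. The analysed number is 225 × 0.80 = 180 per arm, used below.

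**Step 1: size of a pure selection gap.** Assumed, not from the documents: 40% of the intervention arm use the service; its true effect is zero; an underlying normal propensity to use correlates r with the outcome; there is no baseline adjustment. The expected user minus non-user difference, in SD units, is

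gap = r × φ(z) / [p(1 − p)], with p = 0.40, φ(z) = 0.386 and p(1 − p) = 0.24, so gap = 1.61 × r.

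With 180 × 0.40 = 72 users and 108 non-users, the standard error is about √(1/72 + 1/108) = 0.152.

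| r | Spurious gap (SD) | Chance of p < 0.05 |
|---|---|---|
| 0.1 | 0.16 | 18–19% |
| 0.2 | 0.32 | 56–57% |
| 0.3 | 0.48 | 89–90% |

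The lower percentage uses this standard error. The upper allows for the slightly smaller variance within each group and agrees with 2,000 simulated trials per setting (19%, 57%, 90%). At r = 0.2 the gap already exceeds the 0.3 SD the trial is sized to detect.

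**Step 2: an instrumental estimate per service.** The simple estimator is the intention-to-treat (ITT) effect divided by uptake of the service. If the whole system moves the outcome by 0.3 SD and a service with no effect is used by 40%, the estimate for that service is 0.3 / 0.4 = 0.75 SD. The whole system's effect is loaded onto one service.

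**Step 3: both estimators together.** A simulation of 2,000,000 participants per scenario used two services opened by one randomization. Service A was used by 50% and service B by 69%. A shared unmeasured factor correlated 0.5 with propensity to use each service and 0.5 with the outcome. All of these values are assumed.

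| Scenario | True effect of A | Users vs non-users of A, within arm | ITT / uptake of A |
|---|---|---|---|
| Neither service works | 0 | 0.40 | 0.00 |
| Only B works (0.30) | 0 | 0.44 | 0.41 |
| Only B works, use unrelated to the shared factor | 0 | 0.00 | 0.41 |
| Only A works (0.30) | 0.30 | 0.70 | 0.30 |

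The user contrast is wrong whenever selection is present. The per-service instrumental estimate is right in the first and last rows, where no other service affects the outcome. The third row shows that failure of exclusion alone biases it: 0.30 × 0.69 / 0.50 = 0.41. The article's own statement that the services interact makes the favourable condition hard to defend.

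**The case against.** The best defence has three parts. First, the analysis is exploratory, is worded as an association, and sits beside an admission that services are not chosen at random. Second, an article condenses: one sentence naming CACE may be lay shorthand for an instrumental or principal-stratification analysis set out elsewhere. Third, the uptake and selection correlations above are assumed, and adjusting for the baseline score would shrink the gaps.

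All three stand in part. They limit the consequence and mean the figures illustrate rather than predict. They do not make the stated contrast a complier effect, and a correctly run per-service version would still need strong assumptions that one randomization does not supply.

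Three stronger readings might be inferred and are not supported.

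- **That modelling both use and intensity must worsen collinearity.** The article says of that approach "This should reduce multi-collinearity issues in regression analysis". The text does not say that a use indicator and an intensity measure enter the same regression. If they did, the variance inflation would depend heavily on how intensity is coded; trial calculations ranged from about 1.25 to above 30. No finding is made here.
- **That the planned look at server data repeats the error.** The text after Table 3 will explore "whether participants who used Elder Tree the most had better outcomes". That is an openly exploratory, whole-system question and claims no CACE.
- **That the trial's main conclusions are compromised.** The primary and secondary hypotheses rest on the comparison of randomized groups.

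**Conclusion.** The point holds as a mislabelled exploratory analysis that should be corrected. The contrast described is as-treated. A per-service complier effect is not identified from this trial's randomization without strong added assumptions, chiefly that no other part of the package affects the outcome. This follows from the design and does not depend on the illustrative numbers.

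The size of the error in this trial cannot be known from the document. Under the stated assumptions, a service with no effect would show a gap of 0.16 to 0.48 SD between users and non-users, or 0.75 SD by the per-service instrumental route if the whole system had an effect of 0.3 SD and 40% used the service.

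**What to change.** 1. Define one exploratory CACE, for Elder Tree as a whole. Use randomized arm as the instrument, count any use of the system as compliance, and include the baseline score and the stratification factors (region, own device, living alone) as covariates. A use threshold above any use would strain exclusion again, because people below it could still benefit.
2. State the exclusion assumption and its weak points. Assignment also brings, where needed, a computer and Internet service, together with a home training visit and staff calls. These could act on outcomes outside use of the system, so the whole-system estimate is conditional as well.
3. Report service-level comparisons of users with non-users as non-randomized associations within the intervention arm, adjusted for baseline, and do not call them CACE.

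The cost is a change of wording and one two-stage model, with no new data. The downside is that no causal statement can then be made about any individual service.
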